**Fig. 1 Fig1:**
[figure not shown]
Flow diagram study design

**Table 1 Tab1:** Schedule of enrolment, assessments, and intervention training

Study phase	Baseline period		Intervention training period					Follow-up period	
	**Enrollment**	**Allocation**	**Centralized training**	**Supervised training**	**Outcomes assessment**	**Supervised training**	**Outcomes assessment**		
**Timepoint (week)**	**-1**	**0**	**1–2**	**3–8**	**8**	**9–14**	**14**	**18**	**22**
**Enrollment and baseline survey data collection**									
Eligibility Criteria screening	**√**								
Informed consent	**√**								
General demographic characteristics	**√**								
Sleep quality evaluation	**√**								
Neurophysiological assessments	**√**								
Plantar pressure, biomechanical balance, and physical function assessments	**√**								
Randomization		**√**							
Allocation		**√**							
**Interventions training**									
Standardized TCPS group (TCPS posture with abdominal breath adjustment)			**√**	**√**		**√**			
Sham-control *Post Standing* group I (TCPS posture with natural chest breath adjustment)			**√**	**√**		**√**			
Sham-control *Post Standing* group II (normal standing posture with abdominal breath adjustment)			**√**	**√**		**√**			
Sham-control *Post Standing* group III (normal standing posture with natural chest breath adjustment)			**√**	**√**		**√**			
**Feasibility and compliance evaluation**									
Training self-evaluation log			**√**	**√**		**√**			
Training sign-in sheet			**√**	**√**		**√**			
Physical activity, sedentary time, and sleeping time			**√**	**√**		**√**		**√**	**√**
**Safety evaluation**									
Adverse events			**√**	**√**	**√**	**√**	**√**		
Serious adverse events			**√**	**√**	**√**	**√**	**√**		
**Efficacy outcome evaluation**									
Sleep quality (PSQI, ISI)		**√**			**√**		**√**	**√**	**√**
Quality of life (SF-36)		**√**			**√**		**√**	**√**	**√**
**Mechanism outcomes assessment**									
The bioelectrical activity generated by the CNS		**√**			**√**		**√**		
Plantar pressure and biomechanical balance		**√**			**√**		**√**		
Respiratory function		**√**			**√**		**√**		
HRV		**√**			**√**		**√**		
Blood pressure		**√**			**√**		**√**		
Blood oxygen saturation of blood		**√**			**√**		√		

*Abbreviations: CNS* central nervous system, *TCPS Three-circle Post Standing*, *PSQI* Pittsburgh Sleep Quality Index, *ISI* Insomnia Severity Index, *SF-36, 36*-Item Short Form Health Survey Questionnaire, *HRV* heart rate variability

### Sample size estimation

Sample size calculations were performed a priori using G-Power Software (v3.1.9.7, Germany). Due to limited previous studies on the use of *Post Standing* or other Qigong exercises in participants with insomnia, the effect size calculation was based on the best available data regarding the hypothesized change in PSQI score found in the literature. The PSQI effect size ranged from 0.31 to 0.83, so we adopted a conservative estimate of 0.31 for our calculation [44]. An F-test ANOVA (repeated measures, within-between interaction) was used for four groups and three measurements. The desired power was set at 80%, with a two-sided α error probability of 0.05. This resulted in a required sample size of 80 participants. Considering a potential attrition rate of 20%, we aim to recruit a minimum of 100 participants for this study. To allocate an equal number of participants to each arm (1:1:1:1), a minimum of 25 participants per arm is necessary.

### Eligibility criteria

This study aims to recruit full-time college students aged 18 to 26 with normal hearing and right-handedness who meet the Diagnostic and Statistical Manual of Mental Disorders, Fifth Edition (DSM-V) criteria for insomnia disorder. They must have sleep difficulties at least three times per week for a minimum of three months, with impaired daytime functioning and a PSQI score above 5 and an ISI score above 7. Participants must be willing to participate, understand study requirements, and provide informed consent in accordance with the Declaration of Helsinki. The inclusion and exclusion criteria are shown in Table 2.

**Table 2 Tab2:** Inclusion and exclusion criteria

Inclusion criteria	Exclusion criteria
**Eligible participants who meet the following criteria will be included: Participants matching any of the following criteria will be excluded:**	
• Full-time college students, aged between 18 and 26 years • Right-handed, either sex • Normal or corrected to normal hearing	• Engaging in long-term regular practice (regular practice defined as a frequency of at least three times a week and at least 30 min per session) of *Post Standing* or other traditional Chinese mind–body exercises, or any kind of physical activity and muscle strength training at least six months prior to study enrollment
• Fulfilling the diagnostic criteria for insomnia disorder (including difficulty in initiating sleep, maintaining sleep, or early morning awakening with inability to return to sleep, complaints of impaired daytime functioning and sleep difficulty occurring at least three times per week for a minimum of 3 months) according to the DSM-V	• Being in a member of martial arts, dance, aerobics, sanda, taekwondo, and other similar clubs or associations
• PSQI score > 5 and ISI score > 7 • Willing to participate in the study and understand and provide signed informed consent forms according to the Declaration of Helsinki	• Presence of secondary insomnia caused by smoking addiction, drug or alcoholic abuse or dependence, stress disorder, personality disorder, psychoactive substances and non-addictive substances, neurological or psychiatric disorders or other underlying diseases or symptoms such as cervical spondylosis, fever, cough, and pain symptoms
• Able to understand the study process, complete weekly sessions/modules of the intervention program on a regular basis, cooperate with the scale assessments and measurement of EEG, plantar pressure and biomechanical balance, and physical function	• Presence of another sleep–wake disorder (e.g., narcolepsy, restless leg syndrome, a breathing-related sleep disorder, a circadian sleep–wake rhythm disorder, a parasomnia) • Irregular learning and living schedules over the prior four weeks such as staying up late or internet addiction • Have a history of chronic headache and migraine, primary and secondary brain injury, head trauma, and familial psychosis • Taking any medication or healthcare products or receiving other sleep-related non-pharmacotherapy to improve sleep quality at least two weeks prior to study entry • Suffering from malignant tumors or other serious consumptive diseases, autoimmune diseases, infectious diseases, neurological or psychiatric disorders, serious organic disease, or other chronic physical diseases including cardiovascular disease, pulmonary, renal, hepatic or gastrointestinal disease, or hematopoietic system diseases, musculoskeletal system diseases, or other contraindications to exercise • Pregnant, breastfeeding, or planning to conceive within the study period
	• Implantation of active metal or pacemaker or defibrillator in the body that affects measurement and assessment • Skin integrity at the electrode placement site is impaired or allergic to electrode gel or adhesive • Unable to perform breath training due to the onset of acute respiratory disease or other reasons • Participated in any other academic studies or clinical trials in the past 8 weeks or participating in any other academic studies or clinical trials during the study period • Any other circumstances that the investigators believe may make the participant unable to complete, comply with, or unsuitable for this study

*Abbreviations: DSM-V* Diagnostic and Statistical Manual of Mental Disorders, Fifth Edition, *PSQI* Pittsburgh Sleep Quality Index, *ISI* Insomnia Severity Index, *EEG* electroencephalogram

## Intervention training methods

### Standardized TCPS group (TCPS posture with abdominal breath adjustment)

Standardized TCPS group training will consist of three elements: body, breath, and mind adjustments. As seen in the standardized *TCPS* shown in Fig. 2, body adjustment consists of ball encircling training, which requires holding the arms as if embracing a tree, with the palms facing inward about two feet from the chest. The participants look forward or slightly downward and chooses a high, medium, or low stance, depending on individual fitness. The feet are planted firmly on the ground as if standing on a well stone; deep rooted and unshakable. Breath adjustment starts with a normal natural breath and gradually transitions to abdominal breathing and reverse abdominal breathing, with a slower respiratory rhythm and rate and increased volume and depth as the posture gradually lowers. Mind adjustment requires concentrating on the three circular configurations with a relaxed demeanor.

**Fig. 2 Fig2:**
[figure not shown]
The posture and body adjustments of standardized TCPS

## Sham-controlled Post Standing group I (TCPS posture with natural chest breath adjustment)

Sham-controlled *Post Standing* group I also consists of three elements: body, breath, and mind adjustment, where the body and mind adjustment training are the same as the standardized TCPS exercise. However, breath adjustment requires mainly using natural chest breathing and then only regulating breathing to make it slow, fine, and continuous.

## Sham-controlled Post Standing group II (normal standing posture with abdominal breathing adjustment)

Sham-controlled *Post Standing* group II training again contains the three elements of body, breath, and mind adjustment. Here, body adjustment requires standing erect in a natural manner with a step sideways with the left foot such that the two feet are shoulder-width (or a little wider) and parallel with each other. The knees will be bent slightly, the hips relaxed, and the abdomen contracted. Arms will be hung loosely at the subject’s sides, with the palms facing inwards and elbows slightly bent. The fingers will be spread apart and the fingers slightly bent at the joints so that the palms are cupped and about 15 cm from the body. Breathing training is the same as standardized *TCPS*, and mind adjustment requires concentrating on the normal standing posture with a relaxed demeanor.

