Compared to pharmaceutical and psychological interventions, TCPS prioritizes holistic psychological wellness and emotional stability. It offers a proactive and self-practiced approach that allows individuals to regulate their own mind–body connection, unlocking their inner potential without constraints of time or space [22]. This makes TCPS a convenient and safe exercise for enhancing emotional stability, improving sleep health, and preventing psychosomatic disorders. However, there are currently few high-quality clinical studies of the effects of TCPS on insomnia. We have therefore designed a rigorous sham-controlled double-blind clinical trial with the primary objective of evaluating the efficacy of TCPS for treating insomnia in college students. Secondary objectives included assessing plantar pressure and biomechanical equilibrium, respiratory patterns, and resting-state brain activity in individuals engaging in TCPS. In conducting this comprehensive neurophysiological and pathophysiological analysis, we aim to evaluate whether individuals meet standards of TCPS and investigate the underlying mechanisms by which TCPS may impact insomnia.

This study aims to: (1) assess the feasibility, safety, and clinical efficacy of TCPS on sleep quality and quality of life in college students with insomnia in the sham-*Post Standing* controlled double-blind setting; (2) explore the neurophysiological mechanisms underlying the mind adjustments occurring in TCPS associated with insomnia by investigating the functional connectivity between brain regions through resting-state electroencephalography (EEG); (3) investigate the impact of body and breath adjustments in TCPS on the physical function of college students with insomnia by evaluating respiratory function, heart rate variability (HRV), blood pressure, and oxygen saturation; and (4) assess the long-term efficacy of TCPS in terms of sleep quality and quality of life.

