Our primary hypothesis is that TCPS will improve sleep quality and quality of life of college students with insomnia compared with students engaging in sham-controlled *Post Standing* practice and that it will be safe, acceptable, and feasible. Our secondary hypotheses are that (i) the mind adjustment of TCPS will increase alpha and theta frequencies in specific brain regions, particularly in the alpha band, and enhance functional connectivity prior to observable improvements in sleep quality; and (ii) engaging in TCPS will modulate HRV, respiratory function, blood pressure, and oxygen saturation due to body and breath adjustments. Ultimately, we also expect TCPS to improve sleep quality and overall quality of life of students with insomnia following the intervention.

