## Sham-controlled Post Standing group III (normal standing posture with natural chest breath adjustment)

Sham-controlled *Post Standing* group III training has the same requirements as sham-*Post Standing* group II training, except for breathing adjustment training, which will use natural chest breathing and then only regulating breathing to make it slow, fine, and continuous.

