#### Neurophysiological assessment

A resting EEG is a graphical representation of the electrical activity of a group of brain cells. It is obtained by recording and amplifying the brain's spontaneous biopotentials from the scalp using advanced electronic equipment [24–27]. This study will use the Nuamps 40-channel EEG system and Curry 7 acquisition software (Compumedics, Charlotte, NC, United States). The sampling frequency will be set at 1000 Hz and the band-pass filter ranges from 0.01 to 100 Hz. EEG data will be preprocessed using the EEG MATLAB toolkit in MATLAB (R2012a, MathWorks, Natick, MA, United States). Power spectrum analysis will be used to measure the EEG, which quantifies the activity in different frequency bands of delta (2–4 Hz), theta (4–8 Hz), alpha1 (8–10.5 Hz), alpha2 (10.5–13 Hz), beta1 (13–20 Hz), beta2 (20–30 Hz), and gamma (30–40 Hz). The relative and absolute power levels of these frequency bands will be evaluated to assess brain activity and the basic neurophysiology of mind adjustment during TCPS. The study will also explore correlations within and between the hemispheres as well as the functional coupling between different brain areas to investigate the mechanisms underlying the effects of TCPS on insomnia.

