#### Synchronous detection procedure

Different groups of participants will be required to follow the pre-recorded guided voice instructions to practice body, breath, and mind adjustments in sequence. It should be noted that all participants at baseline will simply imitate the training practice under the pre-recorded guided voice instructions. Synchronous detection, including plantar pressure and biomechanical balance, physical function, and neurophysiological assessments, will be performed during the three-minute resting and relaxed standing state before the training practice state with self-active adjustment, the five-minute standing practice state with self-active adjustment, and the three-minute resting and relaxed standing state after the standing practice state with self-active adjustment. The stability of the instrument during the synchronous detection procedure will also be recorded.

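### Focus target follows posture in all four arms, so the design cannot test the hypothesis crediting the EEG change to the mind adjustment of TCPS

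*Protocol article*

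**What the plan says.** The intervention sections of the protocol article define mind adjustment by what the participant concentrates on.

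- Standardized TCPS group: "Mind adjustment requires concentrating on the three circular configurations with a relaxed demeanor".
- Sham group I: breathing differs, "where the body and mind adjustment training are the same as the standardized TCPS exercise".
- Sham group II: breathing is as in TCPS, but "mind adjustment requires concentrating on the normal standing posture with a relaxed demeanor".
- Sham group III: as sham group II, "except for breathing adjustment training, which will use natural chest breathing".

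The Introduction then splits expected effects by component. Hypothesis (i) reads "Our secondary hypotheses are that (i) the mind adjustment of TCPS will increase alpha and theta frequencies in specific brain regions", and goes on to expect enhanced functional connectivity. Hypothesis (ii) assigns heart rate variability, respiration, blood pressure and oxygen saturation to body and breath. Aim 2 is to "explore the neurophysiological mechanisms underlying the mind adjustments occurring in TCPS associated with insomnia" using resting-state EEG. The Neurophysiological assessment section says that the band powers "will be evaluated to assess brain activity and the basic neurophysiology of mind adjustment during TCPS". Study setting and procedure names EEG as a primary outcome alongside the PSQI. Statistical analysis plans group-by-time comparisons of TCPS with the shams, and comparisons over time within TCPS.

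**The concern.** Hypothesis (i) is causal: one named component of TCPS is to change the EEG. To test it, some comparison must vary that component while posture and breathing are held fixed, or at least not vary it in lockstep with one of them. The arm descriptions suggest that no such comparison exists. If so, higher alpha or theta in TCPS than in sham II would fit a posture effect, a focus effect or both; against sham III, a breathing effect would fit as well. Hypothesis (i) as worded would report any of these as an effect of mind adjustment, and it would do so for a primary outcome. The article's Discussion itself allows another source, since it links modulation of brain function to combining the posture with abdominal breathing.

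**Working it through.** The plan gives no figure on this point, so the check is structural.

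**Inputs.** Code each arm from its own section: posture (1 = TCPS), breath (1 = abdominal), focus (1 = three circles).

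| Arm | Posture | Breath | Focus |
|---|---|---|---|
| TCPS | 1 | 1 | 1 |
| Sham I | 1 | 0 | 1 |
| Sham II | 0 | 1 | 0 |
| Sham III | 0 | 0 | 0 |

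**Step 1, correlations between arms.** The posture and focus columns are identical, so their correlation is 1.0. Posture with breath gives 0, and so does focus with breath.

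**Step 2, pairwise contrasts.** Subtract rows:

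| Contrast | Posture | Breath | Focus | What differs |
|---|---|---|---|---|
| TCPS − I | 0 | 1 | 0 | breath |
| II − III | 0 | 1 | 0 | breath |
| TCPS − II | 1 | 0 | 1 | posture + focus |
| I − III | 1 | 0 | 1 | posture + focus |
| TCPS − III | 1 | 1 | 1 | all three |
| I − II | 1 | −1 | 1 | all three |

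Of six contrasts, 0 isolate focus, 2 isolate breath, 2 change posture plus focus, and 2 change all three.

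**Step 3, any other contrast.** The matrix of intercept, posture, breath and focus has rank 3, not 4. The only contrast free of posture and breath main effects is their interaction, (0.5, −0.5, −0.5, 0.5) in the order TCPS, I, II, III. Its loading on focus is 0.5×1 − 0.5×1 − 0.5×0 + 0.5×0 = 0.

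**Step 4, group by time.** Take 4 arms at 3 visits (baseline, weeks 8 and 14), with an intercept, two visit terms, three arm terms, and trained posture and trained breath switched on after baseline. That is 1 + 2 + 3 + 2 = 8 columns, with rank 8. Adding trained focus makes 9 columns and the rank stays 8, so focus adds no estimable term.

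**Step 5, within TCPS.** Over the visits, the three adjustments are trained together. At baseline, participants imitate the practice under the recorded guidance, so change from baseline also bundles them.

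**Step 6, recording windows.** The Synchronous detection procedure has three minutes of rest, "the five-minute standing practice state with self-active adjustment", and three minutes of rest. Taken as whole windows within TCPS, posture, breath and focus are all off, on, off: rank 2, an intercept plus one joint practice effect. In the rest windows all arms stand relaxed, but at weeks 8 and 14 they still differ jointly in trained posture and trained focus. The guidance does take participants through body, breath and mind one after another. No mind-only segment is stated, and any late segment would also carry the posture, the breathing and elapsed time.

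**The case against.** The strongest reply has four parts.

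First, a reader might infer that the protocol credits the EEG change to mind adjustment alone. It does not use that word. The Discussion says that the shams separate body from breath, which they do, and never says that they isolate mind. This stands, and the point does not rest on that reading. It rests on hypothesis (i) naming mind adjustment as the cause while hypothesis (ii) gives the other physiology to body and breath.

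Second, a reader might take aim 2 and the Neurophysiological assessment section as the same causal error. They can equally be read as matching an instrument to each adjustment: EEG for mind, just as the next section pairs plantar pressure with body and respiratory measures with breath. The Discussion also cites earlier work relating connectivity to the mind adjustment of Qigong, which supports EEG as a marker. This stands, so those two places need a note only.

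Third, a reader might infer that no recording could ever help. That is too absolute: because the adjustments are practised in order, early and late parts of the practice recording might differ in focus with posture held, and a fuller document could define such segments. This stands as a limit on the claim, but the evidence would be weak for the reasons in step 6.

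Fourth, the circles are formed by the stance, so the overlap is partly inherent, and every arm has some mind adjustment with relaxation. Both are true. Coding focus by its target compares two kinds of mind adjustment, not its presence with its absence; since no arm lacks it, the arms offer no presence-versus-absence comparison either. An inherent overlap is a reason to change the attribution, not the arms.

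**Conclusion.** The point holds for hypothesis (i). No between-arm contrast (0 of 6) and no time comparison within TCPS separates mind adjustment from posture, and the recording procedure states no mind-only segment. Because the arms fix this, a later analysis of the same arm contrasts cannot recover it.

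The conclusion assumes that the arm descriptions are complete on focus target and that mind adjustment means the instructed focus, as those sections define it. The size of any mind effect is not given, so the possible misattribution cannot be expressed as a number.

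A reader might infer that the efficacy result is undermined. It is not: the PSQI comparison of TCPS with the shams and the two breathing contrasts are untouched, and the separation of body from breath holds if body is understood to include its accompanying focus. What is at risk is the mechanistic reading of a primary outcome, which is worth correcting before results are known.

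**What to change.** 1. In hypothesis (i), attribute the expected rise in alpha, theta and connectivity to the TCPS posture together with its three-circle focus, or to the whole TCPS package.
2. State what the contrasts test: TCPS v sham I and sham II v sham III test breathing; TCPS v sham II and sham I v sham III test posture plus focus; none tests mind adjustment separately.
3. At aim 2 and in the Neurophysiological assessment section, add only a note that EEG serves as a marker of the mind-adjustment component and that the effect of this component is not separately identified.

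The cost is wording. Arms, training, visits, measurements, tests and sample size do not change. The sponsor gives up a claim about mind adjustment that the design could not have supported.
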